### Statistical analysis

The main content of the analysis consists of effectiveness analysis and safety analysis. The analysis of all continuous variables will be presented as mean, standard deviation (SD), median, quartile spacing, and maximum and minimum values. The analysis of all dichotomous variables will be presented as rate, constituent ratio, and hazard ratio. We will use the *t* test and chi-squared test, analysis of variance, and univariate and multivariate logistic regression analysis to describe our data. The factors (*P* <0.15) in univariate analysis will be analyzed in multivariate analysis. All data will be checked twice by two independent statisticians. The two independent statisticians will also be blinded to treatment assignment. We will perform post-hoc subgroup analysis to identify potential significant factors based on age, sex, tumor location, clinical stage of tumor, resection scope, duration of surgery, the volume of intraoperative bleeding, and pathological stage of tumor. Demographics and clinical characteristics of the subjects are summarized as mean ± SD for continuous variables and as number (percentage) for categorical variables. The difference between groups will be considered statistically significant if the *P* value is less than 0.05. All data will be analyzed by using SPSS (software version 25.0; SPSS Inc., Chicago, IL, USA).

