**Methods:**

A total of 400 participants with non-small cell lung cancer undergoing video-assisted thoracoscopic surgery (VATS) lobectomy and systematic mediastinal lymph node dissection (MLND) will be randomly assigned to one of two groups: group A (500 mL pleural lavage fluid) and group B (3000 mL pleural lavage fluid). The primary outcomes include the levels of leukocytes, neutrophils, and inflammatory factors on the first postoperative day. The secondary outcomes include (i) the levels of leukocytes, neutrophils, and inflammatory factors on the second and third postoperative days; (ii) the incidence of postoperative fever on the first, second, and third postoperative days; (iii) the volumes of chest drainage within the first 3 operative days, the duration of drainage, and postoperative hospitalization; and (iv) the incidence of postoperative complications (incision infection, pain, atelectasis, hemorrhage, etc.) and the incidence of pleural effusion requiring thoracic puncture or drainage within 30 days after surgery. The main content of the analysis includes effectiveness and safety analysis. We will perform subgroup analyses to identify potential influence factors.

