### Sample size

This is the first study that focuses on the effect of different volume of pleural lavage on the clinical outcomes following VATS lobectomy and MLND, and no reference is available to estimate the sample size. We estimated the power on the basis of the Student’s *t* test of the levels of leukocytes on the first postoperative day in each group. We estimate an effect size of 0.5 from our experience. A total of 400 participants will be recruited in this study (200 in each group). Judging from our experience, we set the dropout rate at 10% to account for inability to complete the treatment, data errors, loss to follow-up, and other unanticipated study problems. Given a type I error rate of 5%, this study could provide a power of 99.72% by using G*Power (software version 3.1.3, University of Düsseldorf, Germany).

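### The multivariate logistic model takes its terms by univariate P<0.15, with no fixed covariates and no statement that lavage group is kept, so results for retained factors tend to be over-optimistic

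*Protocol article*

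**What the plan says.** The rule is in the protocol article, Statistical analysis. Among the methods listed is "univariate and multivariate logistic regression analysis to describe our data", and the next sentence fixes how the multivariate model is built: "The factors (*P* <0.15) in univariate analysis will be analyzed in multivariate analysis".

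Three related statements matter:

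- **Significance.** The section's only significance threshold comes in a sentence beginning "The difference between groups will be considered statistically significant if the" and is P below 0.05. It is worded for group differences, not for factors in the logistic model.
- **Candidate factors.** No list is given for the logistic model. The only list of patient factors in the section belongs to the subgroup analysis: "age, sex, tumor location, clinical stage of tumor, resection scope, duration of surgery, the volume of intraoperative bleeding, and pathological stage of tumor".
- **Outcomes.** Under Primary and secondary outcomes, the primary outcomes are continuous blood levels compared by mean difference. The binary outcomes are secondary: fever on each of three days, complications, and effusion needing puncture or drainage.

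The article does not say whether lavage group is subject to the screen or always kept.

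**The concern.** A Wald P value and its confidence interval assume that the model was fixed before the outcome was seen. Here a factor is in the model only because it already showed P<0.15 against the same outcome in the same patients. The right reference distribution for a retained factor is the one conditional on passing that screen, and the standard output ignores this. A reader of the multivariate table would take a P value or odds ratio for a retained factor at face value, although both tend to look stronger than they should.

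Two further consequences follow. The data choose the adjustment set, so it can differ from one binary outcome to the next, and adjusted results for fever, complications and effusion would not share a common basis. And because the text leaves open whether the arm is screened, it also leaves open whether an adjusted odds ratio for 3000 versus 500 mL will exist for every outcome.

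**Working it through.** **Inputs from the protocol article.** Sample size: 400 recruited, 200 per group, 10% dropout, "Given a type I error rate of 5"%, standardised difference 0.5, stated power 99.72%. Statistical analysis: entry at univariate P<0.15; significance at P<0.05, carried over to the model as an inference.

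**The plan's own figure.** Evaluable per group: 200 × 0.9 = 180. Noncentrality: 0.5 × √(180/2) = 4.743; df = 358; two-sided 5% critical value 1.967. Noncentral-t power is 99.72%, as stated. This concerns the t test on leukocytes, and the screen does not touch it. It shows that 360 is the evaluable size the plan had in mind, so 360 is used below.

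**Analytic value.** For a null factor independent of the others, the univariate P value is uniform and the multivariate P value is close to it. Hence

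Pr(P<0.05 | entered) ≈ 0.05 / 0.15 = 33%.

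**Simulation of patient factors.** Assumptions, since the article gives none: eight patient factors (the length of the subgroup list) plus a null arm; event rate 10% or 30%; correlation between factors 0 or 0.3; one factor with log-odds 0, 0.2 or 0.3 per SD and seven null factors; 1,500 trials per scenario. Each term was screened at P<0.15, and the survivors were fitted together and tested at P<0.05. The comparator is a full model with no screen.

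| Quantity | With screen | Full model |
|---|---|---|
| Null factor P<0.05, given entry, correlation 0 | 31–35% | – |
| Null factor P<0.05, given entry, correlation 0.3 | 8–20% | – |
| Null factor P<0.05, over all candidates | 2.2–5.3% | 4.9–5.6% |
| At least one false factor among seven nulls | 13–31% | 29–32% |
| True factor, mean estimate, truth 0.2 | 0.229–0.374 given entry | 0.205–0.210 |
| True factor, mean estimate, truth 0.3 | 0.290–0.407 given entry | 0.304–0.318 |

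As ratios to the truth, given entry, the lowest is 0.290/0.3 = 0.97 and the highest 0.374/0.2 = 1.87. With independent factors the range is 1.10–1.87. Given entry and P<0.05, it is 1.18–2.35.

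**The arm.** If lavage group is always kept, its type I error in the same simulations is 4.1–5.1%.

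If it were screened like any other factor, the picture changes. Assumptions: 180 per arm, baseline event rate 10% or 20%, one independent prognostic covariate (log OR 0.6 per SD), seven null factors, true arm log OR −0.4, 3,000 runs per setting. Ranges are over repeated runs.

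| Baseline event rate | Arm retained | Mean log OR if retained | Ratio to −0.4 |
|---|---|---|---|
| 10% | 34–35% of trials | −0.79 to −0.83 | 2.0–2.1 |
| 20% | 48–50% of trials | −0.63 to −0.64 | 1.6 |

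With the arm always kept, the mean is −0.41 to −0.42.

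**The case against.** The strongest reply is that the rule does little harm where it counts. The section says logistic regression serves to describe the data. The primary comparison is a difference in means, and binary outcomes have their own chi-squared test, so no group comparison has to pass the screen. That stands: a null result for fever or complications would still be reported as rates with a test.

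The false-positive argument also has a limit that must be granted. Over all candidates the screen does not raise the per-factor error, and the unscreened full model produces at least as many false factors (29–32% against 13–31% for at least one). Removing the screen makes the reported P values and estimates mean what they claim. It does not lower the count of false findings.

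Three stronger readings are tempting and are not supported:

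- **That the plan screens the randomised arm.** The section uses the word factors for patient and surgical characteristics and groups for the arms. It neither states that the arm is screened nor excludes it, so the arm figures above are conditional on one reading.
- **That the plan tests retained factors at 0.05.** The threshold sentence concerns differences between groups. It is the only threshold given, so carrying it over is reasonable, but it is not written. The Abstract's sentence, "We will perform subgroup analyses to identify potential influence factors", concerns subgroup analyses and does not bear on the screen.
- **That adjusted estimates are always exaggerated.** With correlated factors, 30% events and log-odds 0.3, the mean given entry was 0.97 times the truth. Correlation is plausible here, for example between clinical and pathological stage, so the one-third figure may lie at the high end.

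It can also be said that covariate sets are commonly left to an SAP or full protocol. That would answer a missing list. It does not answer a definite selection rule that is stated in the text, which a later document would have to contradict.

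**Conclusion.** The concern holds as a point about the secondary, adjusted analyses. The entry rule makes inference for retained factors over-optimistic as a tendency. An entered null factor shows P<0.05 in about one third of cases if factors are independent and in 8–20% at correlation 0.3, against a nominal 5%; true effects averaged 0.97–1.87 times their value given entry. Unconditional per-factor error stays near or below 5%. The adjustment set can vary by outcome.

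If the arm were screened, which the text leaves open, its adjusted odds ratio would be lost whenever the crude P is 0.15 or more, and would tend to be exaggerated (1.6 to 2.1 times on the log scale in the settings tried) when retained. The primary mean differences, the chi-squared comparisons and the stated power are unaffected.

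The sizes rest on assumed event rates, correlations, effects and number of candidates. The direction for independent factors follows from the rule itself.

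**What to change.** Delete the P<0.15 sentence. For each binary secondary outcome, specify one logistic model that always contains lavage group plus a short prespecified set of preoperative covariates already collected, for example age, sex, clinical stage and tumour location. Report the arm's adjusted odds ratio with its 95% CI whatever its P value. Restrict the set to preoperative variables: duration of surgery arises after randomisation, and the Background itself expects a large lavage volume to lengthen the operation. If a search for risk factors is still wanted, label it exploratory.

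The cost is a change of wording in one paragraph and no new data; Trial status says recruitment had not opened. The small downside is that some non-prognostic covariates may stay in the model, so the set must be very short for rare complications.

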## Background

In pulmonary surgery, pleural lavage is routinely performed before closing the chest wall, to rinse off residual tumor cells and tissues and ideally prevent pleural implantation of tumor and postoperative infection [1]. Decades ago, it was known that even if there were no obvious malignant pleural effusion or pleural implants, tumor cells could be found in as much a third of postoperative pleural lavage [2]. Since then, accumulating data have indicated the presence of tumor cells in intraoperative pleural lavage as an independent prognostic factor [3–5]. Intraoperative pleural lavage cytology detected before closure could present a higher prognostic value than pleural lavage cytology detected before thoracotomy. Furthermore, it could guide the choice of adjuvant chemotherapy for lung cancer patients after surgery.

Although there is no guideline regarding how pleural lavage should be conducted [6], usually it involves irrigating the thoracic cavity with 0.9% sodium chloride injection varying from 20 to 2000 mL [2, 7–9] at 38~40 °C [10]. However, there are no determinant criteria on the volume of pleural lavage fluid. If the volume of pleural lavage is too small, the residual tumor cells and tissue cannot be washed away, which may result in increased absorption of inflammatory mediators, fevers, and even severe inflammatory reactions [11]. It could affect prognosis and prolong hospitalization [12]. Furthermore, the residual tumor cells may increase the risk of recurrence [13] and metastasis [14–16]. If the volume of pleural lavage is excessive, it will cause waste of resources and prolongation of operation time. Kaneda et al. [9] found that doses of over 500 mL could cause false-negative results of pleural lavage cytology. Considering clinical practice and the literature [7, 8], we decided to test two volumes of pleural lavage: 500 and 3000 mL.

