#### Inclusion criteria

Patients who meet all the following criteria at the start of the treatment are eligible for this study: (i) patients between 18 and 75 years of age, (ii) patients undergoing planned VATS lobectomy and MLND, (iii) be American Society of Anesthesiologists grade I or II, (iv) essential materials such as clinical staging of lung cancer and medication were complete, (v) confirmed diagnosis of NSCLC through pathological examination after surgery, and (vi) willing to participate after reading and signing an informed consent form.

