### Randomization and blinding

Randomization of trial participants will be based on computer-generated random numbers prior to surgery. The random numbers will be printed and placed in consecutively numbered and separate sealed opaque envelopes, which will be opened only when a patient is enrolled and meets all inclusion criteria. The principal doctor (CL) will assign the participant to a group on the basis of the number. The research assistant should receive the notification in a timely fashion and assign patients to their study group strictly as required. This study will be single-blind. The participants will be blinded to the allocation of the participants, whereas the investigators and project manager will be unblinded. If an unexpected emergency occurs, allocation will be disclosed to the investigators, the participant will be withdrawn from this study, and a detailed explanation will be recorded if unblinding happens.

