## Discussion

It is essential to flush the thoracic cavity before chest wall closure. However, scant data could be found in the literature. The most frequently used method is to flush the thoracic cavity with 0.9% sodium chloride injection heated nearly to the temperature of the human body at 38~40 °C. No determinant criteria on volume of pleural lavage fluid have been built. If the volume of pleural lavage is too small, the residual tumor cells and tissue cannot be washed away, which may result in increased absorption of inflammatory mediators, fever, and even severe inflammatory reactions and will affect prognosis and prolong hospital stay. Furthermore, the residual tumor cells may increase the risk of recurrence and metastasis. If the volume of pleural lavage is too high, it will cause waste of resources and prolongation of operation time.

The study will enroll 400 NSCLC patients undergoing VATS lobectomy and MLND and divide them into two groups. This study aims to find out whether different volumes of pleural lavage fluid (0.9% sodium chloride injection) have different effects on prognosis of NSCLC patients measuring by some important clinical indices such as the plasma levels of leukocytes, neutrophils, inflammatory factors, and the incidence of fever after operation were observed 1 to 3 days after operation.

However, the study has some limitations. First, it is a single-center trial, which will restrict its generalizability, so a multiple-center large-sample clinical trial is warranted in the future. Second, the anesthesiologist and surgeons in charge of the intraoperative part of the study cannot be blinded to this study group regarding the safety. Third, the hospitalization time may be different across participants, which may bring effects on the prognosis of patients with NSCLC. Fourth, larger patients may need different volumes of pleural lavage.

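### Duration of surgery is listed as a subgroup factor, although it is measured after randomization, includes the lavage, and by the protocol's own account lengthens with larger volumes

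*Protocol article*

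**What the plan says.** Under Statistical analysis the protocol article states: "We will perform post-hoc subgroup analysis to identify potential significant factors". It then names eight factors: age, sex, tumor location, clinical stage, and "resection scope, duration of surgery, the volume of intraoperative bleeding, and pathological stage of tumor". The same section sets one general significance rule for differences between groups, that the P "value is less than 0.05".

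Four other places bear on this list:
- **Randomization and blinding:** "Randomization of trial participants will be based on computer-generated random numbers prior to surgery".
- **Intervention:** the chest is flushed with 500 mL (group A) or 3000 mL (group B) before the chest wall is closed, that is, during the operation.
- **Background:** "If the volume of pleural lavage is excessive, it will cause waste of resources and prolongation of operation time". The Discussion repeats it: "If the volume of pleural lavage is too high, it will cause waste of resources and prolongation of operation time".
- **Inclusion criteria:** "patients undergoing planned VATS lobectomy and MLND".

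**The concern.** A subgroup comparison keeps the protection of randomization only if the assigned arm cannot influence which subgroup a patient falls into. Duration of surgery fails that condition. It is known only after allocation, it contains the time spent on the lavage, and the protocol expects a large lavage to lengthen it.

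Some group B patients will be classed as long operations only because of the extra lavage time. They move from the short to the long stratum, and their counterparts in group A stay in the short one. If longer, harder operations go with higher inflammatory markers, group B then has easier operations than group A in both strata. With no true effect, group B would show slightly lower markers in each, which could be read as a consistent benefit of 3000 mL.

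Resection scope raises a different and lesser point. Entry requires planned VATS lobectomy, so there is little planned variation to divide patients by.

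**Working it through.** **1. The plan's own figure.** The Sample size section states 99.72% power for day-1 leukocytes. With effect size 0.5, 200 per group less 10% dropout (180 per group) and a two-sided 5% t test, exact noncentral-t power is 99.72%. The figure is reproduced, and the subgroup list does not touch it.

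**2. Inputs for the bias.**
- From the protocol: the direction of the effect on operating time; 180 evaluable per group.
- Assumed, because the protocol gives no values: 3000 mL adds s = 2, 5, 10 or 15 minutes; duration SD 40 minutes; correlation r = 0.2 or 0.4 between duration without extra lavage time and leukocytes; no true effect of volume; a split at the pooled median.

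**3. Formula.** Let z be the standardized duration without the extra lavage time, δ = s/40 and c = δ/2. A patient is in the long stratum if z > c in group A, or z > -c in group B. With truncated-normal means, the spurious difference (group B minus group A, in SDs of leukocytes) in the long stratum is

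b = r × [φ(c)/Φ(c) - φ(c)/(1 - Φ(c))],

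and by symmetry it is the same in the short stratum.

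For s = 10: δ = 0.25, c = 0.125, φ(c) = 0.3958, Φ(c) = 0.5497. The bracket is 0.720 - 0.879 = -0.159, so b = -0.032 at r = 0.2 and -0.064 at r = 0.4.

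**4. Type I error per stratum.** A median split leaves about 90 per arm per stratum, so SE = √(2/90) = 0.149 SD. With k = |b|/SE, the two-sided error is Φ(-1.96 + k) + Φ(-1.96 - k).

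| Added time (assumed) | b, r = 0.2 | b, r = 0.4 | Type I error, r = 0.2 | Type I error, r = 0.4 |
|---|---|---|---|---|
| 2 min | -0.006 | -0.013 | 5.0% | 5.1% |
| 5 min | -0.016 | -0.032 | 5.1% | 5.5% |
| 10 min | -0.032 | -0.064 | 5.5% | 7.1% |
| 15 min | -0.048 | -0.095 | 6.2% | 9.8% |

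**5. Simulation check.** With 180 per arm, no true effect and 3,000 runs per setting, shifts of 0.125 and 0.25 SD (5 and 10 minutes at SD 40) gave differences of -0.014 to -0.063 SD, in line with the table. A shift of 0.5 SD (20 minutes, beyond the range above) with r = 0.4 gave about -0.125 SD and a per-stratum error of about 14%. A treatment-by-stratum interaction test rejected in 4% to 6% of runs in every setting, because the bias is nearly equal in the two strata and cancels.

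**The case against.** The strongest reply is that this is a small flaw in an analysis the protocol itself calls post-hoc and aims at potential factors. Background and Discussion speak of an excessive or too high volume. They give no minutes and do not say that 3000 mL is excessive. If the extra volume adds only 2 minutes, the bias is about 0.01 SD, against a planning effect of 0.5 SD. This stands and limits the size of the point. It does not remove it, because group B receives six times the volume of group A within the measured interval.

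A reader might infer more from the same text, in three ways that it does not support:

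- **That spurious subgroup findings are nearly certain.** Eight factors times ten primary markers is 80 tests, and 80 independent tests at 0.05 would give at least one false positive with probability 98.3%. But the protocol does not say that subgroups will be run on all ten markers, and the markers are not independent. One independent test for each of the eight factors gives 33.7%.
- **That no interaction test or multiplicity rule is planned.** The article is silent on both, and such detail is commonly left to an analysis plan, which is not shown. The 0.05 rule is general and is not tied to subgroups.
- **That resection scope is constant, or a source of bias.** Eligibility fixes the planned operation only; what is performed may still vary. A nearly empty subgroup is uninformative and does not itself bias anything.

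Intraoperative bleeding and pathological stage are also known only after randomization, but nothing in the protocol says that the lavage changes them.

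**Conclusion.** The point holds for duration of surgery and is minor. The protocol names as a subgroup factor a post-randomization variable that contains the intervention and that it says is lengthened by large volumes. Arm comparisons within duration strata are therefore not randomized comparisons.

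Over the assumed 2 to 15 minutes, the bias is about -0.01 to -0.10 SD in both strata, favoring 3000 mL if longer operations go with higher leukocytes. Per-stratum type I error is about 5% to 10%. The direction follows from the protocol together with the assumed positive correlation; the size rests wholly on the assumed shift, SD and correlation.

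Resection scope is a poor choice because it has little planned variation, and for no stronger reason. The label post-hoc sits badly with a list fixed in advance, but that is a matter of wording.

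**What to change.** - Remove duration of surgery from the subgroup list. If operating time up to the start of lavage is recorded, use that instead; the article does not list it as a data item.
- Drop resection scope.
- Describe the remaining factors as pre-specified and exploratory.
- Judge each by a treatment-by-factor interaction test on day-1 leukocytes, the endpoint used for the power calculation. Report the effect with a 95% CI at each level, and draw no conclusion from P<0.05 within a subgroup.

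The cost is a change of wording, and the article states that recruitment had not opened. What is given up is one biased and one largely uninformative subgroup. Interaction tests are less sensitive: with 90 per arm at each of two levels, a difference of 0.5 SD between the two effects has SE 2 × √(2/180) = 0.211 and power Φ(0.5/0.211 - 1.96), about 66%. That suits an exploratory analysis.
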